***SPIRIT Guidance: Recruitment***

*15 Strategies for achieving adequate participant enrolment to reach target sample size*

All patients fulfilling the eligibility criteria and providing informed consent are eligible for this study. Going by the projections, it is expected to enroll substantial number of participants from clinical facilities. A coordination group has been created on digital platform for immediate response to queries, learning from each other’s experiences, and continuity of operations. However, if health system indicates creep, investigators could recruit patients self-isolating at homes. Upon identification by site investigators in the hospital, this cohort would be contacted by trained researchers and data collectors via phone and if informed consent is obtained, recruited. The allocated treatment medicines for 14 days would be delivered. Similarly, swab samples and other clinical information would be collected from participants’ homes in case they cannot travel for testing. All other clinical data would be collected via phone and entered directly into the IT module. The unused or used drug packaging will be collected from participants’ homes upon completion of recruitment period of testing negative on PCR whichever comes first. It is expected that a wider pool of both hospitalized and home-isolated patients would be enough to meet the estimated sample size within the given timeframe.

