**Abstract**

Objectives

To evaluate the effectiveness of Hydroxychloroquine Phosphate/Sulfate (200 mg orally 8 hourly thrice a day for 5 days) *versus* oseltamivir (75 mg orally twice a day for 5 days) *versus* Azithromycin (500 mg orally daily on day 1, followed by 250 mg orally twice a day on days 2-5) alone and in combination (in all seven groups), in clearing the coronavirus (COVID-19) nucleic acid from throat and nasal swab and in bringing about clinical improvement on day 7 of follow-up (primary outcomes).

Trial Design

An adaptive design, set within a comprehensive cohort study, is chosen because it permits flexibility in this fast-changing clinical and public health scenario. The randomized study will be a multicenter, multiarm, multistage, randomized controlled trial with a parallel design. An observation only cohort will emerge from those not consenting to randomization.

Participants

Eligible will be newly diagnosed patients, either hospitalized or in self-isolation, without any comorbidities or with controlled chronic medical conditions like diabetes mellitus and hypertension. Participants of any gender or age group having tested positive for COVID-19 on Real-Time qRT-PCR (Quantitative Reverse Transcription PCR) will be invited to take part in study at twelve centers across nine cities in Pakistan. Those pregnant or lactating, severely dyspneic or under respiratory distress, already taking a treatment, and with serious co-morbidities like liver or kidney failure will be excluded.

Intervention and Comparator

A total of seven comparator groups will be formed: Each drug (Hydroxychloroquine Phosphate/Sulfate, Oseltamivir and Azithromycin) given as monotherapy (three groups); combinations of each of two drugs (three groups); and a final group on triple drug regimen.

Main Outcomes

The laboratory-based primary outcome will be turning test negative for COVID-19 on qRT-PCR on day 7 of follow-up. The clinical primary outcome will be improvement from baseline of two points on a seven-category ordinal scale on day 7 of follow-up.

Randomization

Participants will be randomized, maintaining concealment of allocation sequence, using a computer-generated random number list of variable block size into multiple intervention groups.

Blinding

Computerized allocation to treatment group will be done upon adding participants demographic details and confirmation of informed consent. Neither physician nor participants will be blinded.

Sample Size

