***Methods: Participants, interventions, and outcomes***

**4 PARTICIPANTS**

***SPIRIT Guidance: Study setting***

*9 Description of study settings (eg, community clinic, academic hospital) and list of countries where data will be collected. Reference to where list of study sites can be obtained*

Study sites comprise major public-sector tertiary care health facilities and Covid-19 field hospitals being setup within province of Punjab. Hospitals in other provinces and federal areas will also be invited for participation. Households with self-isolating individuals could also participate in the study. A list of hospitals with confirmed participation has been attached as **Annex 3.**

***SPIRIT Guidance:*** *Eligibility criteria*

*10 Inclusion and exclusion criteria for participants. If applicable, eligibility criteria for study centers and individuals who will perform the interventions (eg, surgeons, psychotherapists)*

Eligible will be newly diagnosed patients without any comorbidities or those with controlled chronic medical conditions, e.g. diabetes mellitus and hypertension. Participants of either gender or age group having tested positive for COVID-19 on qRT-PCR (Quantitative Reverse Transcription PCR) will be invited to take part. Participants who are pregnant or lactating, are already taking any treatment, under respiratory distress or severely dyspneic, have liver and kidney failure will be excluded from the study. Each participant will undergo baseline investigation i.e., liver function tests, renal function tests, urinalysis, and Complete Blood Count; at the time of enrollment. However, diagnostic facilities and hospital admission criteria could vary across cities. A case report form (CRF) has been developed for this proposal and **attached** at the end of this document.

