***SPIRIT Guidance:***

*11c Strategies to improve adherence to intervention protocols, and any procedures for monitoring adherence (eg, drug tablet return, laboratory tests)*

Administration of drugs to participants will be directly observed by the clinical staff at the study sites. Each of the site team has been trained to maintain a record of pharmaceutical supplies from stock entries to disposition. All supplies are labelled NOT FOR SALE from the source. The site teams will be responsible to project demand corresponding with the rate of recruitment, monitor appropriate usage, and maintain a folder of used drug packaging for site audits.

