***SPIRIT Guidance: Sample size***

*14 Estimated number of participants needed to achieve study objectives and how it was determined, including clinical and statistical assumptions supporting any sample size calculations*

This is an adaptive design and parameters for formal sample size calculation in a new disease of a previously unknown virus are not available. Then the sample size and power analysis are indicative for review at each stage of adaptive design. In a standard two-arm, head-to-head trial, the sample size would have been as follows: in order to detect a difference in the laboratory-based primary outcome of 10% (assuming a 50% of participants receiving Hydroxychloroquine Phosphate/Sulfate turn test negative at day 7 and expected rates in comparator groups of 60%), at a significance level 5% and a power of 90%, a sample size of approximately 520 subjects in each group will be required. This sample size will be enough to detect a small-medium difference (Cohen’s d 0.3, a significance level 5% and a power of 90%) in the clinical primary outcome. Additional considerations will need to make for the interim analysis at every stage of the adaptive design. Interim analysis will review sample size according to time to clearance also. Planned blinded sample size re-estimations will need to be undertaken in which we will constantly re-examine the original sample size assumptions. We will aim to maintain the trial power at 90% even if the original sample size assumptions turn out to be far from the observed data. The adaptation at each stage will allow us to drop out fewer promising interventions and will prevent an underpowered trial for the most promising interventions. As the planned modifications will be undertaken in a blinded fashion, there will be no increase in the type I error rate.

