***SPIRIT Guidance: Implementation***

*16c Who will generate the allocation sequence, who will enrol participants, and who will assign participants to interventions*

Randomization sequence was created using Sealed Envelope Ltd 2019 and was stratified by study center and age using random block sizes of 28 and 42 sizes into seven treatments (11). Before randomizing, recruiting physician will confirm eligibility and obtain written informed consent from the participant. Upon entering participant’s demographic details in the IT module, a unique patient ID for the said center and treatment arm would be allocated automatically meaning the recruiting physician has no control over assigning intervention.

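### Comparisons between a dropped and a continuing arm are open to confounding by care setting and calendar time, because home recruitment is conditional and the analysis is not limited to concurrently randomised patients

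*Protocol*

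**What the plan says.** **Who is recruited.** The Abstract states: "Eligible will be newly diagnosed patients, either hospitalized or in self-isolation". Study setting (SPIRIT item 9) adds: "Households with self-isolating individuals could also participate in the study". Neither attaches a condition. Recruitment (item 15) does: "if health system indicates creep, investigators could recruit patients self-isolating at homes". No date, stage or cap is given. It continues: "Upon identification by site investigators in the hospital, this cohort would be contacted by trained researchers and data collectors via phone".

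**How care differs by setting.** Under the adherence item (11c): "Administration of drugs to participants will be directly observed by the clinical staff at the study sites". For home patients, the Recruitment section has medicines delivered and clinical data other than swabs taken by phone.

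**How patients are allocated.** The Implementation section (item 16c) says the sequence "was stratified by study center and age using random block sizes of 28 and 42 sizes into seven treatments". Sequence generation (item 16a) names age only. Neither names hospital or home.

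**How arms leave the trial.** Sample size (item 14): "The adaptation at each stage will allow us to drop out fewer promising interventions". Statistical methods (item 20) sets the first stage at 10% of the total sample.

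**How arms are compared.** Statistical methods gives an odds ratio between groups by intention to treat. Adjustment is for covariates drawn from the stratification factors, and only if baseline imbalance is seen. The stratified analyses named are by age group and by baseline COVID-19 positivity.

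**The concern.** Randomisation protects a comparison between two arms only over the period in which patients could be allocated to either. If an arm closes and the patient mix then changes, the continuing arm gains patients with no randomised counterpart in the closed one.

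Three features of the protocol combine here. The home share can move with health-system load. Arms can close early. The stated analysis has neither a restriction to concurrent patients nor a route by which setting or stage could enter the model, since covariates come from centre and age.

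The protocol itself gives reasons why day-7 results could differ by setting, namely observed against unobserved dosing and bedside against telephone data collection. An odds ratio pooled over stages would then mix drug effect with setting. The Sample size section's assurance that blinded modifications leave the type I error unchanged does not address this.

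**Working it through.** **1. The plan's own figure.** Inputs from the Sample size section: 50% against 60% negative at day 7, 5% significance (two-sided per Statistical methods), 90% power. With pooled variance and no continuity correction:

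n = [1.960 × √(2 × 0.55 × 0.45) + 1.282 × √(0.25 + 0.24)]² / 0.10² = 519 per group.

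The stated figure of about 520 reproduces, and power at 520 is 90.1%. The benchmark is a true difference of 10 points.

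**2. When an arm might close.** No total is stated. If it is 7 × 520 = 3640 (assumption), the first stage is 364 patients, or 52 per arm. A closure halfway, at 260, serves as a second case.

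**3. Size of the spurious difference.** Let the dropped arm close at n₁ patients. The continuing arm reaches 520, its home share after the drop is h, and the home-minus-hospital gap in day-7 success is D. With no drug effect and no home patients before the drop:

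spurious difference = [(520 − n₁) / 520] × h × D.

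The values of h and D, the hospital rate of 50% and the absence of home patients before the drop are assumptions; the documents give none of them.

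Middle case, h = 0.50 and D = 0.10:
- n₁ = 52: (468/520) × 0.50 × 0.10 = 0.045. Rates 54.5% v 50%, OR = (0.545/0.455)/1 = 1.20.
- n₁ = 260: (260/520) × 0.50 × 0.10 = 0.025. Rates 52.5% v 50%, OR = (0.525/0.475)/1 = 1.11.

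For type I error at two-sided 5% (normal approximation), the shift is divided by its standard error:
- n₁ = 52: SE = √(0.25/52 + 0.545 × 0.455/520) = 0.073; shift 0.045/0.073 = 0.62; type I error 9.5%.
- n₁ = 260: SE = √(0.25/260 + 0.525 × 0.475/520) = 0.038; shift 0.025/0.038 = 0.66; type I error 10.1%.

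Range over h = 25%, 50%, 75% and D = 5, 10, 20 points:

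| Arm closes at | Spurious difference (points) | OR | Type I error |
|---|---|---|---|
| 52 | 1.1 to 13.5 | 1.05 to 1.74 | 5.3% to 46% |
| 260 | 0.6 to 7.5 | 1.03 to 1.35 | 5.3% to 51% |

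**4. What restriction to concurrent patients does.** Simulation of 20,000 trials with no drug effect, n₁ = 260, h = 0.50, D = 0.20:
- Dropped v all patients of the continuing arm: difference 5.0 points, type I error 26%.
- Dropped v concurrently randomised patients only: 0.0 points, 4.8%.
- Two arms open throughout: 0.0 points, 4.8%.

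If D is zero, or the home share does not change, this source produces no bias.

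**5. The planned stratified analysis.** The first inclusion criterion requires a positive test. Baseline positivity is therefore the same for every participant, and stratifying by it, as worded, separates no one.

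**The case against.** A reader might infer that home patients enter only after arms have been dropped, within the same centre strata as inpatients, and that the resulting comparisons are biased. The documents do not support that.

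- Later entry is not stated. The Abstract and Study setting sections would allow home patients from the first day. What the text shows is an unreconciled condition.
- Home patients are identified through hospital investigators, so entry in that centre's strata is a fair inference, but it is not written.
- Bias needs a shift in home share after an arm closes, a different day-7 outcome by setting, and use of non-concurrent patients. The protocol does not say that a dropped arm will be compared with patients enrolled after its closure.
- Excluding respiratory distress and severe dyspnoea narrows the difference in severity between settings.
- The seven-category scale is not shown, so no argument can rest on how its categories treat hospitalisation.
- Arms open together are balanced on setting in expectation, and the simulation bears this out. Much of the trial's inference is untouched.

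All of these points stand. The further argument, that restriction to concurrent patients can be left to the analysis plan, stands only in part. That plan is not shown and may deal with it. But the protocol does state its rule: groups as randomised, covariates from the stratification factors only, plus a stratified analysis on a constant. Followed as written, that rule brings in later patients and leaves setting out.

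**Conclusion.** The concern holds as an exposure to confounding, confined to comparisons between a dropped and a continuing arm. It is not a demonstrated bias and does not affect arms open over the same period. On the middle assumptions the spurious difference is 2.5 points (closure at 260) to 4.5 points (closure at 52), a quarter to just under a half of the planned 10 points, with type I error near 10%. Those figures rest on assumed home shares and outcome gaps, and the direction reverses if home patients do worse. The inconsistency over home recruitment and the constant stratifier need no assumption, as both are in the text. The change is cheap and worth making.

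**What to change.** - **Statistical methods:** state that each between-arm comparison uses only participants randomised while both arms were open.
- **IT module:** record setting (hospital or home) at randomisation.
- **Statistical methods:** replace the stratified analysis by baseline test positivity with setting, as a prespecified stratified or adjusted analysis.
- **Abstract, Study setting and Recruitment:** reconcile whether home recruitment is unconditional or depends on health-system load.

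A separate randomisation list for home patients is not needed. It would not cure a non-concurrent comparison, and it would thin the strata: about 470 patients over 12 centres is 470/12 ≈ 39 per centre before the split by age, with blocks of 28 and 42.

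The cost is one data field and a few sentences. Comparisons with a dropped arm also lose precision. At a 50% rate, the standard error of the difference goes from about 0.038 to √(2 × 0.25/260) = 0.044 if the arm closed at 260, and from about 0.073 to √(2 × 0.25/52) = 0.098 if it closed at 52.

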**Objectives**

***Primary Objective***

- To evaluate the effectiveness of Hydroxychloroquine Phosphate/Sulfate (200 mg orally 8hr thrice a day for 5 days) versus oseltamivir (75 mg orally twice a day for 5 days) versus Azithromycin (500 mg orally daily on day 1, followed by 250 mg orally twice a day on days 2-5) as monotherapy and in various combinations in clearing the coronavirus nucleic acid from throat and nasal swab and in bringing about clinical improvement on day 7 of follow-up (primary outcomes).

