***Exclusion Criteria***

1. Confirmed absence of SARS-CoV-2 (COVID-19) infection by a negative test result
2. Have chronic conditions such as heart disease, liver and kidney failure
3. Ongoing respiratory distress or severely dyspneic
4. Pregnant or currently lactating female
5. Immunocompromised, atopic and/or systemic disease(s)
6. On other antiviral drugs
7. History of allergy to any of the drugs to be administered in this study

Both recruitment and administration of study drugs will be carried out by any member of the site investigation team. All site teams have been trained accordingly.

***SPIRIT Guidance:*** *Interventions*

*11a Interventions for each group with enough detail to allow replication, including how and when they will be administered*

Participants will be divided into seven intervention groups (A to G) and eighth group (H) comprising non-consenting individuals observed for supportive care (Figure 1). Study physician(s) will administer three drugs as monotherapy (to three intervention arms), in combination regimen of any of the two trial drugs (to three additional arms), and seventh intervention arm comprising all three drugs. The three drugs with respective dosages are - Hydroxychloroquine Phosphate/Sulfate (200 mg orally 8hr thrice a day for 5 days) versus oseltamivir (75 mg orally twice a day for 5 days) versus Azithromycin (500 mg orally daily on day 1, followed by 250 mg orally twice a day on days 2-5)

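### Every drug is specified as a 5-day course, but home-isolated participants are to receive 14 days of allocated medicines, 2.8 times that course, and no visible text reconciles the two

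*Protocol*

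**What the plan says.** **Course length.** The Primary Objective gives hydroxychloroquine as "200 mg orally 8hr thrice a day for 5 days" and oseltamivir 75 mg twice a day for the same 5 days. Azithromycin is 500 mg on day 1, "followed by 250 mg orally twice a day on days 2-5". The Abstract and the interventions section (item 11a) repeat these schedules, and item 11a applies them to the monotherapy, two-drug and three-drug arms.

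**Home supply.** The Recruitment section (item 15) says of patients recruited while self-isolating: "The allocated treatment medicines for 14 days would be delivered". The same section has used and unused packaging collected from the home at a negative PCR or at the end of the period, whichever is earlier.

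**Control of dosing.** The adherence section (item 11c) says: "Administration of drugs to participants will be directly observed by the clinical staff at the study sites". It also requires site teams to "monitor appropriate usage, and maintain a folder of used drug packaging for site audits".

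**Other timing.** The outcomes section (item 12) schedules swabs on days 7 and 14 and follows those still positive at day 7 to day 14 or later. The statistical methods section (item 20) refers to a decision to go on past day 7 of treatment.

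**The concern.** The course length and the quantity dispensed disagree within one protocol. Both are matters for the protocol, so an analysis plan that is not shown would not be expected to settle them. A site that follows the Recruitment section literally leaves more drug in the home than the regimen calls for, in a setting where no directly observed dosing is described. A site checking usage would be comparing a 14-day delivery with a 5-day course.

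Two things are at stake: avoidable exposure to surplus drug, and uncertainty about which course home participants were meant to receive. The second bears on how the treatment effect is described, because the day-7 endpoints fall after a 5-day course has ended but in the middle of a 14-day one.

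**Working it through.** **Inputs.** Daily doses and the 5-day course come from the Primary Objective and item 11a. The 14-day supply comes from item 15, and the swab days from item 12.

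**Ratio.** 14 / 5 = 2.8, an excess of 14 − 5 = 9 days. The protocol gives no ratio of its own to reproduce.

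**Quantity per home participant, as a ceiling if the stated daily dose is supplied throughout:**

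| Drug | Daily dose | 5 days | 14 days | Surplus |
|---|---|---|---|---|
| Hydroxychloroquine | 3 × 200 mg = 0.6 g | 15 doses, 3.0 g | 42 doses, 8.4 g | 27 doses, 5.4 g |
| Oseltamivir | 2 × 75 mg = 0.15 g | 10 doses, 0.75 g | 28 doses, 2.1 g | 18 doses, 1.35 g |
| Azithromycin | 0.5 g on day 1, then 2 × 0.25 g = 0.5 g | 0.5 + 4 × 0.5 = 2.5 g | 0.5 + 13 × 0.5 = 7.0 g | 4.5 g |

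The protocol states no azithromycin dose after day 5. The 7.0 g therefore assumes that the dose for days 2 to 5 continues. As written, a 14-day supply of this drug cannot be filled from the regimen at all.

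**By the day-7 endpoint.** If dosing ran on, the excess would be at most 7 − 5 = 2 days (7 / 5 = 1.4 times the course):
- hydroxychloroquine 2 × 0.6 = 1.2 g
- oseltamivir 2 × 2 = 4 doses
- azithromycin 2 × 0.5 = 1.0 g

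**Arms affected.** Each drug appears in 1 monotherapy, 2 two-drug arms and 1 triple arm, so 4 of 7. Hydroxychloroquine and azithromycin are given together in 1 two-drug arm and the triple arm, so 2 of 7. The triple arm would hold all three surpluses.

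**Does packaging collection close the gap?** One trigger is a negative PCR. The first scheduled follow-up swab is on day 7, so on the stated schedule this trigger cannot act before day 7, two days after the course should have ended. A participant still positive on day 7 next has a scheduled swab on day 14, by which time a 14-day supply could have been used up. The other trigger, the end of the period, is not tied to day 5. Collection therefore lets a site find out afterwards what was used, but does not limit the course to 5 days.

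**Is there a rule for a longer course?** Item 11b covers discontinuation after a suspected reaction, and changes to protocol or dosage through the regulator and its board. It contains no extension rule. The item 20 wording does not define a longer regimen either, and it does not fit a 5-day course, which has no treatment on day 7.

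**The case against.** **Nobody is told to take drug after day 5.** This stands. The course length already says when dosing stops, and the Recruitment section speaks of delivery, not intake. A reader might infer that home patients would be over-dosed, or that the arms would be compared unfairly. The documents show neither: the same delivery sentence covers every arm, and the share treated at home is not given.

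**The protocol has safeguards.** This stands in part. Item 11c makes sites responsible for monitoring usage, item 15 retrieves packaging from homes, and item 12 has the ordinal scale reported on days 3, 5, 7, 9, 11 and 14. Contact with home patients is not by phone alone, since swabs and other information can be collected at the home. These steps reduce the risk, but none sets the quantity or stops dosing at day 5.

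**The 14-day figure may not be the wrong one.** This also stands in part. The item 20 wording and the link between collection and a negative PCR could both fit treatment until clearance. Alternatively, 14 days may be the follow-up length used by mistake as a supply length, which is only an inference. The text establishes that the durations disagree. That three places give 5 days, including the objective and the interventions section, makes 5 days the sensible default but does not prove it.

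**Home recruitment is a fallback.** It is conditional in the Recruitment section: "if health system indicates creep, investigators could recruit patients self-isolating at homes". A reader might see a contradiction with the Abstract, which admits self-isolating patients without that condition. There is none, because eligibility and recruitment strategy are different matters. The same section nonetheless counts on home-isolated patients to help reach the sample size, so the pathway is not idle.

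**Material is missing.** The participant timeline is given only as Figure 1, which is not shown, and neither are the annexes. They might reconcile the durations, but the conflicting sentences would still need correcting.

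**Conclusion.** The inconsistency is real and should be fixed. The regimen is 5 days in the Abstract, the Primary Objective and item 11a. The home supply is 14 days in item 15, which is 2.8 times as long, and item 20 implies treatment past day 7. No visible text brings them together.

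The surpluses of up to 5.4 g hydroxychloroquine, 18 oseltamivir doses and 4.5 g azithromycin per home participant are ceilings on what could be held. They assume supply at the stated daily dose and, for azithromycin, a dose that the protocol does not give. They do not measure drug taken. Confidence is high for the mismatch in the text. An effect on either primary outcome is not shown and cannot be sized without the share treated at home.

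**What to change.** 1. In the Recruitment section (item 15), deliver the allocated medicines for the 5-day course only.
2. In the statistical methods section (item 20), replace the reference to treatment past day 7 with follow-up past day 7.
3. If the clinical team and the regulator confirm that a longer course is intended, leave the supply and instead state the dose and duration of each drug in the Abstract, the Primary Objective and item 11a, including azithromycin after day 5. Item 20 should then be worded to match.
4. Have sites reconcile the packaging returned from homes against the 5-day course (or the longer one, if confirmed).

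**Cost.** Amendment wording, notice to the National Bioethics Committee, and an instruction or short retraining for sites, as item 25 already requires for modifications. There is no new visit or test and no change to sample size or analysis model. Recruitment was under way and expected to continue for at least three months, so the correction would still reach future home recruits.
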